### Ethical approval

The study protocol has been approved by the Independent Bioethics Committee for Scientific Research at Medical University of Gdansk (the project indentification code: 422/2016). All participants will give informed consent before randomization and the information about the trial will be explained to them. They will be informed about potential benefits and adverse events that may occur during this trial.

### Clinical trial registration

The study has been registered in ClinicalTrials.gov which is a database of privately and publicly funded clinical studies conducted around the world (ClinicalTrials.gov Identifier: NCT03940768).

### Statistical analysis

When computing a priori sample size, we assummed that of all existing approaches used in screening and assessment of malnutrition and cachexia, weight loss – among others - is a phenotype always evaluated by international organizations and commonly used tools/surveys [15], that this parameter will serve as pivotal to calculate required sample size. Calculating the mean weight loss (major component of nutritional status) in a 70 kg men and assuming 1:1 allocation ratio and 80% statistical power we evaluated that the number of participants will be 36. Allowing for a withdrawal rate of 20% for the primary outcome we aim to randomly allocate 40 participants to receive either active product or placebo. The required sample size were evaluated using G-power analysis software. Significance level will be 0.05.

The calculations will be carried out with the use of Statistica package by Dell Inc. The descriptive statistics will include averages, medians, standard deviations, maximum and minimum values. In order to check the normality of distribution of populations subject to research, the W Shapiro-Wilk test will be applied. To check the homogeneity of variations of the groups compared, the Brown-Forsythe test will be applied. Then, depending on the type of data and shape of distributions compared, the U Mann-Whitney test, Student’s t-test or a version of Student’s t-test with independent variance estimation will be applied.

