### Study design

In this 12-week, single-centre, randomized, double-blind, and placebo-controlled study, 20 patients with cancer will be treated with probiotics and 20 patients will receive a placebo. The post-allocation clinical and laboratory assessment will be performed at weeks 0, 4, and 12 in all participants (Table 1). Patients in the probiotic group will receive two capsules of Sanprobi IBS® containing 10^10^ CFU of *L. plantarum* 299v for 12 weeks. Participants in the control group will receive placebo (two capsules daily) for 12 weeks. The participants will be recruited to this study by the nutritionist and the surgeon in Nutritional Counselling Centre Copernicus in Gdansk and Medical University of Gdansk (Department of Clinical Nutrition and Dietetics). The researches and participants will be blinded to the group assignment since the probiotic product and the placebo will be completely identical and indistinguishable from one another. The enrolment of participants is presented in Fig. 1.

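### Randomising 40 does not cover the assumed 20% withdrawal: 32 evaluable patients are expected, not the 36 required, and power is about 75–77% rather than 80%

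*Protocol article*

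**What the plan says.** The Statistical analysis section gives the required size as follows: "assuming 1:1 allocation ratio and 80% statistical power we evaluated that the number of participants will be 36". The next sentence adds the allowance for losses: "Allowing for a withdrawal rate of 20% for the primary outcome we aim to randomly allocate 40 participants". The Study design section confirms the split: "20 patients with cancer will be treated with probiotics and 20 patients will receive a placebo". The test level is fixed ("Significance level will be 0.05"), but whether it is one- or two-sided is not stated. The effect behind the 36 is described only in words ("Calculating the mean weight loss (major component of nutritional status) in a 70 kg men").

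The article nowhere says that the 36 already includes withdrawals, or that patients who withdraw will be replaced.

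**The concern.** Three figures stand in two adjacent sentences: 36 needed, 20% lost, 40 randomised. Any two of them fix the third, and the one printed does not match. The number randomised was meant to protect the number needed against the expected loss, and it protects against only half of that loss.

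This calculation justifies the primary comparison, weight loss on probiotic against placebo. A reader who takes the paragraph at face value would treat a non-significant result as coming from a trial with 80% power after withdrawals. On the plan's own withdrawal assumption it would have less.

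**Working it through.** **Inputs, all from the protocol article.** Required total 36, so 18 per arm at 1:1; power 80%; significance level 0.05; withdrawal for the primary outcome 20%; randomised 40, as 20 + 20 (Statistical analysis and Study design). The two-group comparison is by t-test or Mann-Whitney test. A two-sided test is my assumption; the one-sided case is shown as well.

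**Step 1: try to reproduce the 40.**

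- Standard inflation, N/(1 − w): 36/0.80 = 45 (18/0.80 = 22.5, so 23 per arm and 46 in total for equal arms).
- The common shortcut, N × (1 + w): 36 × 1.20 = 43.2, or 44 as an even total.
- Withdrawal that 40 does cover: 1 − 36/40 = 10%.
- Expected evaluable at 20% withdrawal: 40 × 0.80 = 32, or 16 per arm.

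Neither way of inflating gives 40 from 36 and 20%.

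**Step 2: power with 32 evaluable.** The effect and SD are not given as numbers, so I take the plan's statement that 36 gives 80% power and solve for the standardised difference d (difference divided by SD). With n per arm, the t statistic has 2n − 2 degrees of freedom and noncentrality d × √(n/2).

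- At n = 18, 80% power gives d = 0.961 (noncentrality 0.961 × 3 = 2.88).
- At n = 16 with the same d, the noncentrality is 0.961 × √8 = 2.72 and power is 74.9%.

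The normal approximation can be checked by hand. d = (1.960 + 0.842) × √(2/18) = 0.934, and power at 16 per arm is Φ(0.934 × √8 − 1.960) = Φ(0.68) = 75.2%.

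**Step 3: vary what is not stated.**

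| Case | d | Power with 32 evaluable |
|---|---|---|
| Two-sided t, 36 gives exactly 80% | 0.961 | 74.9% |
| Two-sided t, 36 rounded up from just over 34 | 0.991 | 77.4% |
| One-sided t, 36 gives exactly 80% | 0.846 | 75.6% |
| Mann-Whitney, two-sided (relative efficiency 0.955) | 0.985 | 74.9% |

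The second row is the most favourable two-sided case. It uses the largest d for which 17 per arm does not exceed 80% power, so that the calculation would still return 36.

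**Step 4: the effect for which 80% power does hold.** With 16 per arm, two-sided t-test, d must be about 1.02, compared with 0.961 at 18 per arm.

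**The case against.** The strongest reply is that the text shows an inconsistency without showing which figure is wrong. Because 36/0.90 is exactly 40, the 20% may be a slip for 10%; 40 would then leave 36 and the stated power would stand. Equally, 40 × 0.80 is exactly 32, so the 36 could be the slip. This is fair, and it makes the 75–77% conditional on both 36 and 20% being meant. It does not rescue the paragraph, which is wrong under every reading. The 10% reading also needs support: the limitations in the Discussion cite high mortality among cancer patients qualified for home enteral nutrition.

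A second reply is that the Participant timeline section says data will be collected if a participant does not continue, so some who withdraw might still supply weights. But the 20% is attached explicitly to the primary outcome, so as written it already describes losses to that endpoint.

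A third is that the loss is small and the article already lists the small single-centre sample as a limitation. The loss is small, and that stands. The general caveat, however, does not tell the reader that the withdrawal allowance is wrong. Nor should this slip be blamed for the trial being able to detect only large effects: even the intended 36 evaluable patients need about 0.96 SD, and the slip adds about 0.06 SD to that.

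**Conclusion.** The concern holds. Given 36 required and 20% withdrawal, randomising 40 leaves an expected 32 evaluable patients, four too few. Power for the effect the plan was sized on is about 75–77%, a shortfall of 3 to 5 percentage points, and 80% power is reached only at about 1.02 SD.

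The patient counts are plain arithmetic on the plan's figures. The power figures rest on accepting 36 as the number for 80% power at the 0.05 level and on equal losses in the two arms. They do not require knowing the difference or SD used, and they change little with the sidedness or the choice between the t-test and Mann-Whitney test. This is a certain error of modest size in the justification of the primary comparison.

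**What to change.** Rewrite the sample-size paragraph so that its figures agree. The least costly version keeps the design: 40 randomised (20 per arm), 32 expected evaluable at 20% withdrawal, about 75–77% power for the effect on which 36 was based, and 80% power only for a difference of about 1.02 SD. The sponsor can replace the 75–77% range with one value from the inputs of its own calculation.

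If 10% was the rate intended, correct the rate and give the grounds for it; 40 and 80% can then stay. The rate should not be halved merely to fit the 40. If 80% power at 20% withdrawal is to be kept, the number randomised must rise to 45, or 46 for equal arms.

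Either of the first two options changes one paragraph and adds no patients; the first makes the stated power slightly less favourable. The third adds five or six patients, and the article itself says recruitment is difficult.

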### Outcomes

#### Primary outcome

The primary outcome is the prevention of weight loss in a probiotic-receiving group in comparison to a placebo-receiving group.

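### The primary test is picked from the outcome data by normality and variance pre-tests, so the hypothesis and effect measure are not fixed, and 5% is not guaranteed for a difference in means

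*Protocol article*

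**What the plan says.** The Statistical analysis section sets out a two-stage procedure. The normality check comes first: "In order to check the normality of distribution of populations subject to research, the W Shapiro-Wilk test will be applied". A Brown-Forsythe check of equal spread between the groups follows. The choice among three tests is left in these terms: "depending on the type of data and shape of distributions compared, the U Mann-Whitney test". The other two candidates are the pooled and the separate-variance t-tests. The section gives no level for either pre-test and does not say whether normality is judged in each arm or on pooled data. It exempts no outcome.

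The Primary outcome section says only "The primary outcome is the prevention of weight loss in a probiotic-receiving group in comparison to a placebo-receiving group" and names no test of its own. The selection rule therefore governs the primary comparison.

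The sample size is derived from a mean: "Calculating the mean weight loss (major component of nutritional status) in a 70 kg men". With equal arms and 80% power, this led the authors to 36 patients. On the error rate the section says "Significance level will be 0.05".

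**The concern.** The three candidate tests do not ask the same question. Both t-tests compare means. Mann-Whitney compares whole distributions (the probability that a patient in one arm exceeds a patient in the other) and yields no mean weight difference. If pre-tests on the trial's own outcome data decide which one is reported, the primary hypothesis and the effect measure are settled only after the data are seen. The trial was sized on mean weight loss, yet its primary p-value may not be about a mean.

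At this size the pre-tests are also unreliable guides. Shapiro-Wilk sends some truly normal samples to the rank test, and Brown-Forsythe often misses a real difference in spread, which leaves Student's t in use. What is at stake is whether a p-value below 0.05 can be read as evidence of a mean weight difference with the stated 5% error.

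**Working it through.** **Inputs from the protocol.** Alpha 0.05 (sidedness not stated; two-sided taken), power 80%, 1:1 allocation, 36 patients before withdrawals (18 per arm), 40 randomised (20 per arm).

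**Inputs assumed.** The protocol gives no SD, effect size or distribution. Each pre-test is taken at 0.05, with Shapiro-Wilk applied in each arm. The distributions are normal, heavy-tailed (t with 4 df) and lognormal (sigma 0.6), all centred to equal means, with SD ratios of 1 to 2. Arm sizes are 18 v 18, or 20 v 14 to represent uneven losses.

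**The plan's own figure.** The 36 cannot be reproduced without an effect and an SD, but it can be solved backwards. By the normal approximation, n per arm = 2(1.960 + 0.842)²/d². Setting n = 18 gives d = √(2 × 7.85/18) = 0.93. The exact noncentral-t calculation gives d = 0.96. This is a standardised difference in means, and it is used for the power comparison below.

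**Rule simulated.** If Shapiro-Wilk rejects in either arm, use Mann-Whitney. Otherwise, if Brown-Forsythe rejects, use Welch. Otherwise use Student's t. Simulation error is √(p(1−p)/R): about 0.15 points at 5% with 20,000 runs and 0.4 points with 3,000.

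**How often the test switches.**
- Normal data, equal spread, 18 v 18: 9.9% go to Mann-Whitney and 4.0% to Welch, so about 14% leave Student's t although its assumptions hold.
- Heavy-tailed data: about 39% go to Mann-Whitney. Lognormal data: about 83%.
- Normal data, SD ratio 2, 18 v 18: Student's t is still used in about 31%.

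**Type I error, same distribution in both arms.** Normal 4.8%, exponential 4.9%, lognormal 5.2%, t with 3 df 4.9%, uniform 4.6%. This is about 5% throughout.

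**Type I error for equal means, arms differing in spread.**

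| Setting | Planned rule | Welch alone |
|---|---|---|
| Normal, SD ratio 2, 18 v 18 | 5.3% | 4.9% |
| Normal, SD ratio 1.5 to 2, 20 v 14, smaller arm has larger SD | about 6 to 7% | about 5% |
| Same, larger arm has larger SD | about 4 to 5% | about 5% |
| Lognormal, SD ratio 1.5 | about 8 to 9% | about 5 to 6% |
| Lognormal, SD ratio 2 | about 13% | about 6% |

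The 8 to 9% covers two runs, one near 8% and one of 6,000 trials (18 v 18) at 9%. The size moves with the assumed skew. At SD ratio 1.5, milder skew (sigma 0.4) gives 6.7% and stronger skew (sigma 0.7) gives 10.0%, with Welch at 5.0% in both. Still stronger skew at SD ratio 2 gives 16 to 17%, with Welch at 6.2 to 6.3%.

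**Source of the excess.** With lognormal data and SD ratio 2 at 18 v 18, the planned rule gives 13.4% and Mann-Whitney on its own also gives 13.4%.

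**Power at a 0.96 SD shift, equal spread, 18 v 18, unadjusted.** Normal: Welch 80%, planned rule 80%. Heavy-tailed: 81% v 86%. Lognormal: 81% v 92%.

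**The case against.** A reader might infer that pre-testing as such breaks the 5% level. The figures do not support that. When treatment does nothing at all, both arms share one distribution and the rule rejects about 5% of the time. The 13% is the rank test's own rejection rate when scored against a null of equal means that it does not test. In that setting the distributions really do differ, so rejection is not an error for Mann-Whitney's own null. Likewise, the 6 to 7% with normal data needs one particular pairing of arm size and spread, and reverses if the pairing reverses. These points stand, and they limit the error-rate claim to a difference in means.

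It is also true that the protocol gives no skewness, variance ratio or differential loss. The 20 v 14 split and every distribution here are assumptions, and the error figures are illustrations. The protocol's limitations do describe a non-homogeneous group with high mortality, so unequal spread and loss are conceivable, but no size can be read from that.

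Two further objections carry less weight. The paragraph covers all outcomes, and its reference to the type of data may partly concern ordinal or symptom scales. It still makes the choice depend on distribution shape and gives the primary outcome no exemption. A separate analysis plan might fix the test, but what is criticised here is a selection rule that the protocol states, not a detail it leaves out.

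Finally, a fixed comparison of means is not free. Under heavy tails or skew it gives up power that the planned rule gains through the rank test. That stands and belongs in the recommendation.

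**Conclusion.** The point holds in this form. The stated rule leaves the primary hypothesis and effect measure open until the data are seen, although the trial is sized on a mean. That part needs no simulation, because it follows from the wording.

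On the error rate the conclusion is conditional. The level is about 5% for identical distributions. For a difference in means it can rise to about 8 to 9% (SD ratio 1.5) or 13% (SD ratio 2) under lognormal skew of sigma 0.6, and to about 6 to 7% for normal data only if the smaller of two unequal arms has the larger SD. Welch alone stays at about 4 to 7% across these settings. The figures rest on assumed distributions, arm splits and pre-test levels. The defect weakens the interpretation of the primary result; it does not invalidate the trial.

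**What to change.** Stop using Shapiro-Wilk and Brown-Forsythe to select the primary test; they may remain as description. Name one primary analysis in advance: a comparison of mean 12-week weight change between arms, adjusted for baseline weight, with heteroscedasticity-robust errors, or the separate-variance t-test if no adjustment is made. Report the mean difference with its 95% CI. Give Mann-Whitney as a named sensitivity analysis, reported whatever the distribution looks like.

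The change takes about two sentences and no new data, since body mass is already measured at baseline and at 12 weeks. There is no meaningful power loss with normal data. If weight change proves heavy-tailed or strongly skewed, power is about 81% against 86 to 92% for the planned rule at a 0.96 SD shift, before any gain from baseline adjustment. The sponsor should accept that trade knowingly. If a rank-based target is preferred, it should be fixed in advance as the primary hypothesis, and the sample size restated to match.

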**Methods:**

Forty patients with cancer receiving home enteral nutrition will be enrolled in this clinical trial and randomized to receive one capsule of *Lactobacillus plantarum* 299v (Sanprobi IBS®) twice a day or placebo for 12 weeks in a double-blind manner. Laboratory tests (the level of albumin, total protein, transferrin, and total lymphocyte count), anthropometric parameters (body mass, the content of fat mass, muscle mass, and total body water), Nutritional Risk Screening (NRS 2002), enteral nutrition tolerance as well as quality of life will be measured. Measurements will be obtained at the baseline and after 4 and 12 weeks of treatment.

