First, this is a single centre study with small sample size; moreover, the group is non-homogenous. It could take a lot of time to recruit more patients and with the same type of cancer, due to high mortality of cancer patients qualified for HEN. Additionally, not every patients fulfilling inclusion criteria is able to take part in this study. Therefore, there is a need to create a multi-center study to have a better chance for a larger sample size.Second, the participants will intake the capsules at home, so we cannot be completely certain if they will really administer the intervention products.Third, the tolerance of enteral nutrition will be assessed by questionnaire fulfilled by patients at home, thus we cannot be sure if they will do it every day or simply before follow-up visits.

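### The plan names only unadjusted two-sample tests although baseline values are available, and it does not fix the weight variable; the power cost is large only if week-12 weights are compared

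*Protocol article*

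**What the plan says.** The protocol article (Statistical analysis) describes a Shapiro-Wilk check of normality and a Brown-Forsythe check of variances. After these, "depending on the type of data and shape of distributions compared, the U Mann-Whitney test" or one of two t-tests is chosen; the full list reads: "the U Mann-Whitney test, Student’s t-test or a version of Student’s t-test with independent variance estimation will be applied". No other between-arm method is named, and none of the three carries a covariate.

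Under Primary outcome the article states: "The primary outcome is the prevention of weight loss in a probiotic-receiving group in comparison to a placebo-receiving group". It does not say whether the analysed variable is week-12 weight, absolute change or percent change, or whether week 4 or week 12 decides.

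The baseline data are planned. The Abstract lists "anthropometric parameters (body mass, the content of fat mass, muscle mass, and total body water") and adds: "Measurements will be obtained at the baseline and after 4 and 12 weeks of treatment". Study design confirms that "assessment will be performed at weeks 0, 4, and 12 in all participants". Laboratory values, NRS 2002 and WHOQOL-BREF follow the same visits. The tolerance diary is the exception, since no baseline value is described for it.

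The Discussion concedes that "this is a single centre study with small sample size; moreover, the group is non-homogenous".

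**The concern.** Patients with different cancers and of both sexes differ in body weight far more than one patient is likely to change in 12 weeks. A two-sample test on week-12 weight carries all of that between-patient variation as noise, and any chance difference at baseline passes almost whole into the result. A test on change removes most of both. An analysis with baseline weight as covariate deals with both whichever variable is meant.

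The plan commits to tests without a covariate and leaves open which variable enters them. At stake are the power of a trial of 40 patients and the stability of its estimate. The choice of test by pre-test adds a further uncertainty about what will be estimated.

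**Working it through.** **Inputs from the protocol article (Statistical analysis).** Power 80%, allocation 1:1, 36 evaluable patients (18 per arm), 40 randomised. "Significance level will be 0.05"; sidedness is not stated and is taken as two-sided.

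**Input assumed.** The correlation ρ between baseline and week-12 weight is not in the document; the range 0.5 to 0.98 is shown. Variances are taken as equal at both visits.

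**1. The plan's own figure.** The 36 cannot be reproduced, because no mean difference or SD is given. Solving the noncentral-t power equation for 80% at 18 per arm gives a standardised difference d = 0.961 (0.846 if one-sided). Since the calculation is framed as mean weight loss, d is read in SDs of change.

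**2. Relative variances.** With the variance of a single weight set to 1:
- week-12 weight: 1
- change: 2(1−ρ)
- ANCOVA: 1−ρ²
- ANCOVA relative to change: (1−ρ²)/[2(1−ρ)] = (1+ρ)/2

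**3. If week-12 weight is tested.** The same true effect, in SDs of weight, is 0.961 × √(2(1−ρ)):
- ρ = 0.80: 0.961 × 0.632 = 0.608, power 42.6%
- ρ = 0.90: 0.961 × 0.447 = 0.430, power 24.1%
- ρ = 0.95: 0.961 × 0.316 = 0.304, power 14.4%

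**4. If change is tested.** The t-test has 80.0% power by construction. For ANCOVA the effective difference is 0.961/√[(1+ρ)/2 × (1 + 1/(N−4))], with N−3 = 33 degrees of freedom. With N = 36 the small-sample factor is 1 + 1/32 = 1.031.

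| ρ | (1+ρ)/2 | effective d | ANCOVA power | gain over t-test on change |
|---|---|---|---|---|
| 0.50 | 0.75 | 1.093 | 88.9% | +8.9 points |
| 0.80 | 0.90 | 0.998 | 82.8% | +2.8 |
| 0.90 | 0.95 | 0.971 | 80.7% | +0.7 |
| 0.95 | 0.975 | 0.959 | 79.7% | −0.3 |
| 0.98 | 0.99 | 0.951 | 79.1% | −0.9 |

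Simulation (20,000 trials per cell) agrees to within about one point. Mann-Whitney on normally distributed change had about 76% to 77% power at N = 36 (3,000 trials per cell).

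**5. Chance imbalance.** At 18 per arm the standard error of the baseline difference is √(2/18) = 0.333 SD of weight. In a comparison of change, a fraction (1−ρ) of an imbalance carries over. One standard error, as a share of the target effect, is then:
- ρ = 0.80: 0.20 × 0.333/0.608 = 11%
- ρ = 0.90: 0.10 × 0.333/0.430 = 8%
- ρ = 0.95: 0.05 × 0.333/0.304 = 5%

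**6. Secondary measures.** At ρ = 0.5, final value and change both have relative variance 1 and ANCOVA has 0.75, so adjustment saves 25% against either.

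**The case against.** The strongest defence is that the plan already means change. Study aims and Primary outcome speak of preventing weight loss, and the sample size refers to mean weight loss. A t-test on change subtracts the baseline value, so it does use it. At the high correlations plausible for body weight over 12 weeks, ANCOVA then gains a point or nothing. The two-sample tests are valid, because randomisation already accounts for chance imbalance in the type I error. An article may also leave the exact variable to a fuller document. Finally, adjusting for baseline weight does not deal with the mix of cancer types that the Discussion mentions.

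Most of this stands, and it rules out two stronger readings. A reader might infer that the trial gives away most of its power. The documents do not support that: the 43%, 24% and 14% figures hold only if raw week-12 weights are compared, which is the less natural reading. A reader might also infer that a chance baseline difference is typically as large as the effect sought. No target effect in kilograms is stated. On the back-solved effect, one standard error of the baseline difference is 55%, 78% or 110% of the target at ρ of 0.80, 0.90 or 0.95 (0.333/0.608, 0.333/0.430, 0.333/0.304), and in a comparison of change only the shares in step 5 carry over.

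What does not stand is the view that nothing needs changing. The three tests are a stated commitment, not a gap left for an analysis plan, and nothing in the text excludes a week-12 comparison. For the secondary outcomes the wording points to change even less clearly.

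**Conclusion.** The point holds in a limited form and is worth acting on. The plan fixes unadjusted tests where a baseline-adjusted model is available from data already collected, and it leaves the primary variable and visit open. On the likely reading (change in weight) the loss is modest: about 3 points of power at ρ = 0.8, 1 at 0.9, none from 0.95 upward, plus a small residual sensitivity to baseline imbalance. On the less likely reading (week-12 weight) it is severe: about 37, 56 and 66 points at ρ of 0.80, 0.90 and 0.95. For secondary measures with lower baseline correlations the gain from adjustment is larger, about 9 points at ρ = 0.5 for an outcome otherwise powered at 80%.

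These sizes rest on an assumed ρ, an effect back-solved from 36 evaluable patients, a two-sided test and roughly normal data with equal variances. They are for absolute weight and do not transfer to percent change.

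**What to change.** Name week 12 as the deciding visit. Replace the pre-tested choice of test with one primary model: ANCOVA of week-12 weight on treatment and baseline weight, reporting the adjusted difference with a 95% CI. Using absolute change as the response gives the same treatment estimate, so this settles the open variable as well. Name in advance any further prognostic covariate.

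Use the same baseline-adjusted model for body composition, laboratory values and the WHOQOL-BREF domains. Keep the Mann-Whitney and t-tests as supportive analyses.

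The cost is a change of analysis wording. No new data are needed. The statistical price is one degree of freedom, at most about one point of power when the correlation is very high.
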